### Public and community involvement and engagement

A project advisory group (PAG) was established for this project to ensure that the intervention and trial are both meaningful and acceptable to older Chinese adults in the UK. The PAG consists of four PCIE representatives: two leaders of Chinese associations in Manchester, both with nursing backgrounds; a Chinese-speaking physiotherapist; and an older Chinese adult with an interest in PA, all of whom have experience working closely with older Chinese adults in the UK. The PAG group were consulted to ensure the strategies were appropriate. The group contributed to the design of the intervention, the determination of inclusion and exclusion criteria, outcome assessments, progression criteria, and participant recruitment.

### Ethics issue

This study has been reviewed and approved by the University of Manchester Research Ethics Committee 2 (Ref: 2024–19749-37,005). The research will comply with the principles of Good Clinical Practice and will follow all research laws and regulations within England. Participation in this study is entirely voluntary. Enrolled participants will be informed that they can withdraw from the study at any time.

### Intervention fidelity

Fidelity refers to how closely the delivered intervention matches the originally planned or designed protocol [44]. In this study, intervention fidelity reflects the extent to which the three main components of the intervention are delivered as planned. A fidelity checklist will be used to systematically assess these components and will be completed by the lead researcher. The checklist can be found in Appendix 2. Specifically, fidelity is assessed by checking:

Whether all participants in the intervention group receive the culturally tailored PA promotion booklets; Whether the three-monthly workshops are organised and delivered according to the planned time and content; Whether at least three motivational messages are sent to participants via the social media support group as intended each week. Additionally, fidelity monitoring includes recording whether all participants receive a pedometer and resistance band to support home-based exercise.

### Data monitoring and quality assurance

We are collecting and storing personal information in line with the General Data Protection Regulation (GDPR) and the Data Protection Act 2018. A data management plan has been established to ensure that all data is properly documented and securely stored. The lead researcher will be responsible for recruiting all participants, randomising them to intervention or control and collecting research data. All research data will be stored in a secure folder on password-protected, encrypted computers. Access to the data collected during the study is available only to the research team. The key linking real names to pseudonymised data will be stored separately in an encrypted file accessible only to the lead researcher. Pseudonymised data and transcripts will be stored for 5 years following the end of the study.

### Progression criteria

Progression criteria for a full RCT are developed following the guidance of Avery et al. [45]. The thresholds are informed by findings from earlier reflective research [46, 47], internal team discussions, and consultation with the PCIE group. In line with Mellor et al. (2023), we define progression criteria across multiple trial domains, including recruitment, retention, data completeness, fidelity, safety, and intervention acceptability, drawing on both qualitative and quantitative data [48]. Full details of the progression criteria are provided in Table 4.

**Table 4 Tab4:** Progression criteria

Domain	Go-proceed with RCT	Amend-proceed with change	Stop-do not proceed
Recruitment	If at least 30 participants are recruited within eight weeks	If at least 16–29 participants are recruited within eight weeks	If ≤ 15 participants are recruited within eight weeks
Retention	If ≥ 24 participants (80%) complete the 18-week follow-up	If 20–23 participants (64–79%) complete the 18-week follow-up	If ≤ 19 participants (63%) complete the 18-week follow-up
Adherence	If an average of ≥ 12 of the 15 participants (80%) attend each workshop	If an average of 8–11 of the 15 participants (53–73%) attend each workshop	If an average of ≤ 7 of the 15 participants (46%) attend each workshop
Data completeness	If ≥ 90% of the data is completed	If 70–89% of the data is completed	If ≤ 69% of the data is completed
Fidelity	If all core intervention components are delivered as planned	If minor deviations in the delivery of core components	If major deviations in the delivery of core components
Safety	No serious adverse events; minor events, if any, are manageable and anticipated	Some minor adverse events; no serious harm, but may need adjustments	Serious adverse event(s) related to the intervention were reported
Acceptability	Qualitative data indicate strong acceptability of the intervention components	Qualitative data indicate general acceptability, with changes needed	Qualitative data indicate the intervention was unacceptable

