### Sample size

The determination of the sample size is driven by practical considerations and the need to obtain meaningful insights into the feasibility aspects of the larger trial, which is different from estimating effects or hypothesis testing in an RCT that requires robust sample calculation. There is limited guidance on determining the sample size for feasibility trials. A recent review shows that the median target sample size of pilot and feasibility studies was 30 (with an interquartile range of 20–50) per arm [12]. Julious (2005) proposed a rule of thumb of 12 participants per group [13].

Considering the timeline of the project, it is essential to balance sample size requirements with time constraints.

We aim to include at least 12 participants per study arm, totalling 24 participants. To account for an anticipated 20% dropout rate, we will recruit at least 30 participants. Assuming a retention rate of 80% with a sample size of 30, the 95% confidence interval for the number of retained participants is approximately 19 to 27.

This study targets older Chinese adults in the UK with insufficient PA. Chinese as an ethnic minority group in the UK is often considered a hard-to-reach group for research. Based on insights from the PCIE presentations, recruiting physically inactive Chinese adults presents even greater challenges, as those who are used to sedentary lifestyles are reluctant to participate in any activities, including research.

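### Table 4 fixes retention and adherence as head counts that fit only 30 randomised and 15 in the intervention arm, and the adherence bands leave gaps

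*Protocol article*

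**What the plan says.** The Sample size section says "We aim to include at least 12 participants per study arm, totalling 24 participants", and then "To account for an anticipated 20% dropout rate, we will recruit at least 30 participants". It assumes 80% retention of 30 and adds that "the 95% confidence interval for the number of retained participants is approximately 19 to 27".

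Table 4 (Progression criteria) turns this into three-way rules:

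- **Recruitment.** Go is at least 30 in eight weeks. Amend is "If at least 16–29 participants are recruited within eight weeks". Stop is 15 or fewer.
- **Retention.** Go is "If ≥ 24 participants (80%) complete the 18-week follow-up". Amend is "If 20–23 participants (64–79%) complete the 18-week follow-up". Stop is 19 or fewer, labelled 63%.
- **Adherence.** Go is an average of at least 12 of 15 (80%). Amend is "If an average of 8–11 of the 15 participants (53–73%) attend each workshop". Stop is an average of 7 or fewer, labelled 46%.

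The Workshop section schedules three workshops. The Randomisation section uses random blocks of 2, 4 or 6 within gender strata. No section says how the counts change when the sample is not 30 or the arm is not 15, or whether the count or the percentage governs.

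**The concern.** A retention criterion should measure how many of those randomised stay. When it is a fixed count it also measures how many were recruited, which Table 4 already judges in its own row. A recruitment shortfall that the table classes as Amend is then counted again as poor retention and poor adherence. Recruitment above 30 has the opposite effect and makes Go easier to reach.

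The Discussion says that the recruitment criterion is meant to be strict and that the retention and adherence thresholds are meant to be more flexible. Fixed counts work against that intention. Under-recruitment is also foreseeable, because the Sample size section itself stresses how hard inactive older Chinese adults are to recruit.

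The adherence row has a second problem that does not depend on sample size: its bands are whole numbers, but the quantity judged is an average over three workshops.

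**Working it through.** **1. The plan's own figures.** Inputs are from Sample size and Table 4.

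- Recruitment target: 24 / (1 − 0.20) = 30. It reproduces.
- Interval for 24 of 30 retained: the Wilson method gives 18.8 to 27.1, which agrees with the stated 19 to 27.
- Retention labels: 24/30 = 80.0% and 19/30 = 63.3%. The denominator is therefore 30.
- Adherence labels: 12/15 = 80.0%, 11/15 = 73.3%, 8/15 = 53.3%, 7/15 = 46.7%.

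**2. Retention by count at other sample sizes.** The proportion needed is 24/N for Go and 20/N to avoid Stop.

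| N randomised | Needed for Go | Needed to avoid Stop | Verdict at 100% completion |
|---|---|---|---|
| 16 | 150% | 125% | Stop |
| 19 | 126.3% | 105.3% | Stop |
| 20 | 120% | 100% | Amend |
| 23 | 104.3% | 87.0% | Amend |
| 24 | 100% | 83.3% | Go |
| 28 | 85.7% | 71.4% | Go |
| 30 | 80.0% | 66.7% | Go |
| 36 | 66.7% | 55.6% | Go |
| 40 | 60.0% | 50.0% | Go |

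Of the sample sizes checked (16 to 30, and several from 32 to 50), the counts agree with the table's own percentage bands for every outcome only at N = 30. At N = 40, 24 completers is Go at 60.0%, below the table's own 63% Stop label.

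**3. Chance of each retention verdict at 80% true retention.** Let X be binomial (N, 0.8). Stop is P(X ≤ 19) and Go is P(X ≥ 24).

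| N | P(Stop) | P(Go) |
|---|---|---|
| 20 | 0.99 | 0 |
| 24 | 0.54 | 0.005 |
| 28 | 0.09 | 0.31 |
| 30 | 0.03 | 0.61 |
| 40 | 0.00 | 0.999 |

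The true retention is the same in every row; only the number recruited differs. Judged as a proportion at N = 24, Go needs at least 20 (0.80 × 24 = 19.2), so P(Go) = 1 − 0.54 = 0.46. Stop is 15 or fewer (0.64 × 24 = 15.4), with P(X ≤ 15) = 0.04.

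**4. Adherence when the arm is not 15.** Go needs 12/m and Amend 8/m of an arm of size m. For m = 8 these are 150% and 100%; for m = 12, 100% and 66.7%; for m = 20, 60% and 40%. Even at N = 30, the arm is exactly 15 in only about 48–68% of simulated allocations. That simulation used blocks of 2/4/6 in two gender strata, with splits from 15/15 to 20/10 assumed. The arm is nearly always between 13 and 17.

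**5. Adherence with exactly 15.** The average is total attendances / 3, out of a possible 45. Totals of 22, 23, 34 and 35 give averages of 7.33, 7.67, 11.33 and 11.67 (48.9%, 51.1%, 75.6%, 77.8%). None lies in a column. The printed percentages leave the same holes, 46–53% and 73–80%.

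If the 45 attendances are independent, P(total = 34 or 35) is 0.27 at 75% attendance and 0.24 at 80%. With clustering within person (beta-binomial, correlation 0.3 to 0.7 assumed), it is about 0.16 to 0.21. If each person attends all three workshops or none, totals are multiples of 3 and the gap cannot occur.

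**The case against.** The best defence is that the percentages are the real rule and the counts are those percentages worked out for the planned 30. The retention row does not print a denominator, and Sample size ties 80% to a sample of 30. Also, the recruitment row counts people within eight weeks, whereas "we will recruit at least 30 participants" carries no time limit, so 16–29 at eight weeks need not be the final sample. Both points are fair, and they make the retention fault conditional on the final number randomised. They do not remove it. The criterion is worded as a count, nothing gives the percentage priority, and no text promises an extension of recruitment. For adherence the percentages do not help, because they have the same gaps. Rounding to whole participants would close them, but the article does not state it.

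Some stronger readings are tempting but unsupported:

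- **That the printed percentages are wrong.** The label 64–79% is not a failed conversion of 20–23 out of 30. It fills the band between 63% and 80%. Printing 46% for 46.7% is a truncation that changes no verdict.
- **That pooled retention must also be met in each arm.** The 12 per arm in Sample size is a sample-size aim. Table 4 sets no arm-specific retention criterion.
- **That a Stop in one row stops the programme.** No text says that one domain overrides the others. The Discussion says the criteria support decision-making.
- **That an unclassified attendance result is likely.** The figure of 24–27% is the independence case and falls with clustering.

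**Conclusion.** The point holds as a should-fix ambiguity in the decision table. With exactly 30 randomised, the retention row works as written. At other final sizes, reading by count and reading by percentage can give different verdicts. Within the sizes the plan allows, the count reading can give Stop with full completion (16–19 randomised) or Go well below 80% (24 of 36). The probabilities of 0.54 and 0.005 at N = 24 rest on the plan's own 80% retention and on independent completion.

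The adherence gaps need no assumption about sample size, since four attainable averages have no verdict even with 15 in the arm. How often they would arise depends on assumed attendance and clustering: at 75–80% attendance, from zero up to about 27%. No effect estimate depends on either row. What is at stake is a clear progression recommendation, fixed before the data are seen.

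**What to change.** State both rows as contiguous proportions and say that the percentage governs, with counts shown only as an illustration for 30 randomised.

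- **Retention** = participants completing the 18-week follow-up / number randomised. Go ≥ 80%; Amend ≥ 64% to < 80%; Stop < 64%. At N = 30 this gives the present counts exactly: 24 or more, 20–23, 19 or fewer.
- **Adherence** = total workshop attendances / (3 × number randomised to the intervention). Go ≥ 80%; Amend from a lower cut to < 80%; Stop below that cut. The sponsor should confirm the lower cut, which its own labels place between 46% and 53%. Extending Amend up to 80% also settles averages of 11.33 and 11.67, so the sponsor should confirm that too.

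The cost is rewording two rows, with no new data and no change to procedures. It should be done and dated before follow-up results are known, because choosing between count and percentage afterwards would be a post hoc decision.

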## Discussion

This is the first trial known to address physical inactivity among older Chinese adults in the UK, a group often overlooked in mainstream health interventions. Although RCTs are considered the gold standard for assessing the effectiveness of health interventions, it is strongly recommended to conduct a pilot and feasibility study before a full-size RCT [49]. A feasibility RCT ensures that a larger trial will be scientifically sound, ethically justified, and resource-efficient [50, 51]. A feasibility study can also provide information for intervention modification to make it more acceptable to the target population [52].

Progression criteria are developed to assess feasibility, guide trial and intervention modifications, and support decision-making about progressing to a definitive trial. There are no universally agreed-upon criteria or thresholds in the literature, as a single standard is unlikely to suit all studies. It is therefore important to consider the specific context of each trial [48]. For example, Hynes et al. [46] used the successful recruitment of all 20 patients with multimorbidity in primary care (100%) as a criterion for progressing to an RCT, while Young et al. [47] proposed a 50% recruitment rate among people living with frailty and receiving haemodialysis as the threshold for a “go” decision.

The progression criteria in this study are shaped by the characteristics and context of the target population. Although ethnic minority groups, including older Chinese adults in the UK, are often described as hard to reach, the research team has built trust with this community through sustained engagement and previous research activities, which helps ensure successful recruitment. The study specifically targets older Chinese adults who do not currently meet recommended PA guidelines. While eligibility criteria were initially considered as part of the progression plan, findings from earlier research and feedback from the PCIE group confirmed that most older Chinese adults in the UK are physically inactive. This makes the eligibility criteria easily achievable and therefore less critical as a progression indicator for this feasibility study. In addition, compared with traditional clinical trials focusing on medical interventions, behaviour change interventions such as PA promotion are viewed by the PCIE group as more acceptable. This is likely to further support recruitment, retention, acceptability, and safety. Taken together, this context supports the use of relatively strict recruitment criteria, aiming to recruit 100% of the intended sample within the planned timeframe to ensure the feasibility of a future full RCT. More flexible thresholds for retention and adherence allow for appropriate modifications, consistent with the overall objectives of the study. 

The intervention in this trial was developed through in-depth interviews with the target population to ensure its alignment with their cultural values, preferences, and specific barriers to engaging in PA [53]. Utilising the Behaviour Change Wheel, a series of BCTs were identified to enhance participants’ capability, opportunity, and motivation to engage in PA [9, 54]. These techniques were implemented through a package comprising booklets, three workshops, and a social media support group, all tailored to the cultural context of older Chinese adults.

These components were chosen to provide a multi-faceted approach that combines traditional educational materials with interactive and peer-supported elements. The booklets serve as a tangible resource for participants, enabling them to engage with the content at their own pace. This comprehensive package comprises three components: the culturally appropriate core booklet, the Chinese version of the Otago exercise booklet, and the PA logbook. Each page of the core booklet was thoughtfully designed to address capability, opportunity, and motivation-related barriers to PA among older Chinese adults, as summarised in Table 3. Recognising that many participants are unfamiliar with how to perform strength and balance exercises, the Otago exercise booklet, an evidence-based programme proven to prevent falls [55], was translated into Chinese to meet the needs of older Chinese adults in the UK. In addition, a PA logbook was designed to help participants set PA targets, create activity plans, and sustain their PA behaviours. This decision was based on participants’ reported need, as many indicated that PA is not part of their routine. It also aligns with evidence suggesting that goals and planning are effective BCTs for promoting PA among older adults, fostering both motivation and achievement [56].

The social media group is intended to foster ongoing support and engagement. As an ethnic minority group, older Chinese adults in the UK often live in dispersed areas, making it challenging to find exercise buddies in their local communities. Virtual peer support provides an alternative option to address this barrier. It also acknowledges the growing adoption of technology among older adults [57]. Instead of using a single type of social media, as suggested by PCIE activities, participants can choose between WeChat and WhatsApp to enhance the acceptability of the intervention component. Both types of social media have been used to deliver PA interventions in previous studies and have been shown to be well accepted by older adults [58, 59]. This approach could provide valuable evidence for determining the most suitable social media support method for this population in further studies.

### Practical consideration

The study aims to recruit at least 30 participants within a timeframe of 8 weeks. Collaborative efforts have been made to enhance recruitment, including securing support from the Chinese associations. A qualified Chinese-speaking physiotherapist has agreed to lead the group Otago exercises. Additionally, the university will provide a venue for the workshops. By addressing these practical considerations, the study ensures adherence to ethical guidelines, establishes effective recruitment strategies, secures suitable intervention venues, and considers incentives to boost participant engagement.

### Limitations and challenges

The study’s small sample size is a limitation inherent to feasibility studies, which could affect the generalisability of the findings. However, our primary aim is to test the intervention’s feasibility, and the insights gained will be crucial for planning a larger trial. Convenience sampling will be employed in feasibility studies due to its practicality and ease of participant recruitment. This approach may introduce potential bias and limit the generalisability of the findings. To address this limitation and enhance the applicability of the study’s results, we will recruit participants from a wide range of demographics, including diverse genders, ages, language backgrounds, and PA levels. By actively engaging individuals with varied characteristics and activity levels, we aim to gain a comprehensive understanding of the intervention’s feasibility across different subgroups within the target population [60]. Additionally, as with all self-report measures, responses on instruments such as the PASE and COM-B questionnaires may be subject to social desirability bias, potentially influencing the accuracy of reported behaviours and perceptions [61].

### Implications for full-scale RCT

If the progression criteria are met, the study will pave the way for a larger RCT that could have significant public health implications. The results will also inform necessary adjustments to the intervention, such as refining the booklet content, optimising workshop delivery, or enhancing the social media group’s functionality. While this intervention was developed within the UK context, its culturally tailored approach may offer valuable insights for adaptation and scalability in other countries with growing older Chinese populations or other ethnic communities, where cultural sensitivity is key to success.

## Conclusion

This feasibility RCT is a crucial step towards understanding how to effectively promote PA among older Chinese adults in the UK. By grounding the intervention in the lived experiences and cultural contexts of the target population, this study not only tests the feasibility of the proposed strategies but also sets the stage for future research that could lead to meaningful health improvements in this underserved group. The findings from this study will guide the development of a full-scale RCT, with the ultimate goal of creating culturally appropriate, sustainable interventions that improve the health and well-being of older Chinese adults in the UK.

## Trial status

As of the time of manuscript submission, participant recruitment for this study was still in progress.

